### Randomization assignment

This study is designed as a randomized, waitlist-control trial. Eligible participants will be randomly and equally allocated to one of the three groups: T (TJ) group, P (placebo) group, and W (waitlist-control) group. Random Allocation Software (version 1.0.0, Isfahan, Iran) will be used to generate a randomization scheme. The principal investigator (PI) will generate the random allocation sequence, and will not share it with other investigators. After the run-in stage, a research assistant (RA) will assign treatments according to the codes which are kept in opaque sealed envelopes with consecutive randomization numbers. Emergency unblinding can only happen when the intervention information is compulsory for the participant’s future management.

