### Sample size

Sample size calculations are based on the primary outcome measurement. Since this is a pilot clinical study, the improvement rate of group W would obviously be 0. Subsequently, we assume that there will be 30 % improvement of TNSS symptoms in group T and 15 % in group P. Considering a power of 80 %, and a alpha value of 2.5 % (two-tailed), the sample size will be calculated using the following formula:$$ n=\frac{2\lambda }{{\left(2{ \sin}^{-1}\sqrt{P_t}-2{ \sin}^{-1}\sqrt{P_w}\right)}^2}, $$

The λ is the cut-off value. *Pt* is 30 % and *Pw* is 0. Then each group will need at least 38 subjects for significance to be detected [27]. Allowing for a 20 % dropout, we plan to recruit 46 subjects in each group, making a total of 138.

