### Data processing and analysis

All efficacy and safety analyses will be conducted according to the intention-to-treat (ITT) principle. Missing values will be imputed by the last-observation-carried-forward method. The statistical analysis will be performed using the Statistical Packages for the Social Sciences (SPSS) for Windows, version 21.0. Statistical significance is defined as a two-sided *P* value of <0.05. Baseline characteristics will be reported as mean (SD). Comparisons between groups will be conducted by using an analysis of covariance (ANCOVA) with baseline as covariate. All items and subscales will be compared between groups for each 4-week period using ANCOVA, with treatment group as a factor in the model and baseline as the covariate. The changes in scores from baseline to the end-point of treatment will be tested using repeated measure analysis of variance (ANOVA). Within-group differences will be assessed using a paired *t* test for normally distributed data and a Wilcoxon signed-rank test for non-normally distributed data.

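### The sample size states a two-tailed alpha of 2.5 %, but the analysis section sets a two-sided 0.05 threshold with no exception for the primary outcome

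*Protocol article*

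**What the plan says.** The Sample size section bases its calculation on the primary outcome, the change in weekly average TNSS. It sets the error rates as follows: "Considering a power of 80 %, and a alpha value of 2.5 % (two-tailed"). The rates it puts into the formula are those of T and W: "Pt* is 30 % and *Pw* is 0". It also states an assumption for the placebo arm: "we assume that there will be 30 % improvement of TNSS symptoms in group T and 15 % in group P".

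The Data processing and analysis section gives one threshold for the whole trial: "Statistical significance is defined as a two-sided *P* value of <0.05". It compares groups by ANCOVA with treatment group as a factor and baseline as covariate.

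The Objective section names two comparisons, T against the placebo control and T against the waitlist control. The Discussion gives the waitlist arm a further purpose, to gauge the influence of the sham patch, which implies a look at P vs W. The article does not say which comparison decides the trial, whether T must beat one control or both, or whether pairwise tests depend on an overall three-group test.

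**The concern.** The familiar pairing of one-sided 2.5 % with two-sided 5 % does not explain the difference, because the article labels both levels two-sided. Read literally, they are two decision thresholds for one primary outcome. A primary result at P = 0.03 or P = 0.04 would be called significant under the analysis section and not significant at the level stated for the sample size.

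This matters more with two control groups than with one. A level of 2.5 % is what 5 % split evenly over two comparisons would give, and the objective names two. If that was the intention, the blanket 0.05 removes the protection. T vs W is also the comparison in which participants know whether they receive a patch, so a trial called positive on that comparison alone, at the looser threshold, would be weak evidence.

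**Working it through.** **1. Can the stated sample size show which level was used?** Inputs from the Sample size section: Pt = 0.30, Pw = 0, power 80 %, n = 38 per group before dropout. The article's formula is n = 2λ / (2 arcsin√Pt − 2 arcsin√Pw)².

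- The denominator is (2 arcsin√0.30)² = 1.159² = 1.344.
- At two-sided 0.025 with one degree of freedom, λ = 9.51, so n = 2 × 9.51 / 1.344 = 14.1. With two degrees of freedom, λ = 11.49 and n = 17.1.
- At two-sided 0.05, λ = 7.85 gives n = 11.7, and λ = 9.63 (two degrees of freedom) gives n = 14.3.
- To reach 38, λ would have to be 38 × 1.344 / 2 = 25.5.

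The stated 38 does not reproduce at either level, so it cannot show which alpha was used.

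**2. Error rate over the two named comparisons.** Allocation is equal ("Eligible participants will be randomly and equally allocated to one of the three groups"). T vs P and T vs W share arm T, so their test statistics have correlation 0.5. If they were independent, the chance of at least one false positive would be:

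- at 0.05 each: 1 − 0.95² = 9.75 %;
- at 0.025 each: 1 − 0.975² = 4.94 %.

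The shared arm lowers both a little. Simulation of three equal arms with pooled variance (400,000 replicates at 38 and again at 46 per arm) gives:

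| Rule on the primary outcome, all arms equal | Chance of at least one false claim |
|---|---|
| T vs P or T vs W, each at 0.05, no gate | 8.9–9.1 % |
| T vs P or T vs W, each at 0.025, no gate | 4.5–4.6 % |
| Any of three pairs at 0.05, only after an overall test at 0.05 | 5.0 % |
| T must beat both controls, each at 0.05 | 0.9 % (at most 5 % in general) |
| Any of three pairs, each at 0.025, no gate | 6.3–6.4 % |

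The last row shows that 0.025 covers two comparisons, not three.

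**3. How often could the choice of level change the conclusion?** When there is no effect, any one comparison falls between the thresholds with probability 0.05 − 0.025 = 2.5 %. Under the article's own rates, the arcsine approximation gives power Φ(h√(n/2) − z), where h is the difference of the arcsine terms and n = 38:

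- T vs P (0.30 vs 0.15, h = 0.364): about 26 % at 0.025 and 35 % at 0.05, so in about 10 trials in 100 the verdict would depend on which section is followed.
- T vs W (0.30 vs 0): above 99 % at both levels.

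These power figures use improvement rates, as the sample size does. The planned ANCOVA works on scores, so they are only a guide.

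**The case against.** A reader might infer that the trial's false-positive rate is 9 to 12 %. The article does not support this as a fact. It specifies ANCOVA with a three-level group factor, which has an overall test, and it never says that ungated pairwise tests are run or that any one of them is a win. With an overall test first, the rate is about 5 % when all arms are equal. If only one arm differs, a single pairwise null remains true and the error is still at most 5 %. The 12 % end also counts P vs W as a success, and that comparison is not an efficacy claim for Tian Jiu. What stands is the 9 %, and only under its stated conditions.

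A reader might also infer that a deliberate correction for two comparisons was dropped. The article gives no reason for the 2.5 %. It may equally be loose wording for 2.5 % in each tail of a 5 % test, in which case the error lies in the Sample size section. Nor can one say that the trial was sized at 2.5 %, since 38 reproduces at neither level. Stating 0.025 for planning and testing at 0.05 does not by itself inflate error or cost power.

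Finally, the sentence "All items and subscales will be compared between groups for each 4-week period using ANCOVA" invites an argument about many tests. The article already fixes one primary outcome at one time point, and the handling of secondary items may sit in an analysis plan that is not shown. That argument is not part of this point.

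None of this removes the conflict between the two stated levels, which does not depend on anything missing from the article.

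**Conclusion.** The point holds as an internal contradiction: two-sided 2.5 % for the sample size and two-sided 5 % for the analysis, with no exception for the primary outcome and nothing to reconcile them. A primary P value between 0.025 and 0.05 has no settled meaning.

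Its size is conditional. The chance of at least one false positive is about 9 %, against about 4.6 % at 0.025 each, if T vs P and T vs W are tested pairwise, ungated and unadjusted, if either counts as success, and if all arms are equal. Two common rules would hold it to about 5 % or less at the 0.05 threshold, but the article commits to neither. The matter should be fixed, but it does not show that the trial's error rate is out of control.

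**What to change.** State one level and the comparisons to which it applies. Either of these removes the contradiction:

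- **Keep 2.5 %.** In Data processing and analysis, add: *For the primary outcome, T vs P and T vs W are each tested at two-sided 0.025, matching the level stated for the sample size. P vs W and all other comparisons are supportive.* P vs W has to stay outside the 0.025 rule, since three comparisons at that level give about 6.4 %.
- **Keep 5 %.** Correct the Sample size section to two-sided 0.05, revisit the calculation at that level, and state a rule covering the two comparisons. Examples are an overall three-group test before any pairwise test, or a requirement that T beat both controls.

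The edit is one or two sentences, and the Trial status section says that no patient had begun treatment at submission. The first option makes each primary threshold slightly stricter. On the article's own rates, with 38 per arm, power for T vs P falls from about 35 % to about 26 %, while T vs W is hardly affected. Under the second option, requiring T to beat both controls makes the low power of T vs P the limit on success; an overall test first is less demanding.

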### Objective

The aim of this study is to investigate the efficacy of TJ in the treatment of AR, by comparing it with a placebo-control group and a waitlist-control group, in Hong Kong.

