### Outcomes

The primary outcome will be the change in the weekly average of the Total Nasal Symptom Score (TNSS) recorded in participants’ diaries from baseline to the end of treatment [22]. The TNSS consists of four nasal symptoms (rhinorrhea, nasal itching, nasal obstruction, and sneezing) using a five-point scale from 0 to 4 (0 = no symptom, 1 = mild, 2 = moderate, 3 = severe, 4 = very severe). The TNSS will be obtained from the sum of all four individual symptom scores, with a total possible score ranging from 0 (no symptoms) to 16 (maximum symptom intensity). This scoring system has been validated [23, 24].

The secondary outcomes will be changes in symptoms and changes in need for medication between baseline and the end of treatment. Symptoms will be assessed by using the RQLQ, which has 28 questions in seven domains (activity limitation, sleep problems, nasal symptoms, ocular symptoms, other symptoms, practical problems, and emotional function) ranked from 0 (no impairment) to 6 (severe impairment) [25]. Rescue medication need will be measured using an RM score (RMS), comprising the weekly sum of daily assessments. Rescue medicine usage will be scored daily on a four-point scale (0 = no rhinitis medicine; 1 = cetirizine, 10 mg/d, or equivalent; 2 = cetirizine, 20 mg/d, or equivalent; 3 = systemic or topical corticosteroids for AR) (daily range; 0 to 3; weekly range: 0 to 21). If more than one RM is used on the same day, only the maximal score medication will be recorded [26].

For safety concern, we will record every adverse event during the treatment and follow-up, and make statistical comparisons. Treatment will be suspended immediately should serious adverse events occur. Further assessment will be needed to decide whether the trial should be suspended.

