## Discussion

TJ, also known as natural moxibustion is a conventional method of treating respiratory allergic diseases in TCM. The procedure is convenient and inexpensive. Thousands of people accept this treatment in China every year. Laboratory study has found that natural moxibustion treatment can reduce IgE and interleukin (IL)-4 levels in the plasma of asthmatic rats, as well as airway inflammation [28]. Clinical studies have found that TJ can modulate anti-inflammatory cytokines [17], and that it appears to work by neuro-immunological mechanisms. However, there have been no methodologically controlled clinical studies confirming the efficacy of TJ therapy.

Therefore, our team has designed this randomized, single-blinded, controlled trial to evaluate the effectiveness of TJ therapy for AR. To our knowledge, this will be the first study to compare TJ therapy with a placebo-control group, as well as a waitlist-control group.

We use pigmented flour mixed with water to make the sham TJ treatment. However, some articles mention that in many studies, sham acupuncture is equally effective as acupuncture [29, 30]. Although the sham TJ does not have the pharmacological effects, the operating procedures still causes a pressing sensation to the skin. Because we use the same acupoints for both groups, pressing these acupoints may create an effect like the acupressure. Therefore, we have designed the study with three groups. One group (group T) will receive traditional TJ therapy, which means the application of herbal patches to specific acupoints on the skin. A second group (group P) will receive sham TJ therapy, which means the application of patches with an inert, similar appearance to the TJ patch on the same acupoints. A third group (group W) will not receive any treatment material in order to examine the influence of sham TJ on the study results.

The trial protocol is the foundation of every clinical study. To facilitate appropriate reference standards for scientific, ethical and safety issues before the trial begins, the protocol of this study has been developed according to Consolidated Standards of Reporting Trials (CONSORT) statement [31], the Standard Protocol Items: Standards for Reporting Interventions in Controlled Trials of Acupuncture (STRICTA) statement 2010 [32], and Standard Protocol Items: Recommendations for Interventional Trials (SPIRIT) statement 2013 [33].

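### The protocol does not say which contrast decides efficacy, and the tests it names can be significant when Tian Jiu is no better than the sham patch

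*Protocol article*

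**What the plan says.** Throughout, T is Tian Jiu, P the sham patch and W the waitlist. All references are to the protocol article.

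- **Objective.** The aim is to "investigate the efficacy of TJ in the treatment of AR, by comparing it with a placebo-control group and a waitlist-control group". It does not say whether T must beat both comparators or either one, or in what order they are tested.
- **Outcomes.** "The primary outcome will be the change in the weekly average of the Total Nasal Symptom Score (TNSS) recorded in participants’ diaries". The change is measured up to the close of the treatment period, and no contrast is attached to it.
- **Sample size.** It assumes 30 % improvement in T and 15 % in P, and says "the improvement rate of group W would obviously be 0". Only T and W enter the formula: "Pt* is 30 % and *Pw* is 0. Then each group will need at least 38 subjects for significance to be detected". The 15 % for P is not used.
- **Data processing and analysis.** Groups are compared by ANCOVA with baseline as covariate. The next sentence, on items and subscales per 4-week period, gives the model: "using ANCOVA, with treatment group as a factor in the model and baseline as the covariate". A repeated-measures ANOVA follows for changes in scores to the treatment end-point. Significance is two-sided P < 0.05. No pairwise contrast, order or joint requirement is named.
- **Discussion.** The third group "will not receive any treatment material in order to examine the influence of sham TJ on the study results", which is a P versus W question. The same paragraph allows that pressing the acupoints under the sham patch may act like acupressure.

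**The concern.** The three contrasts answer different questions. T versus P isolates the herbs. T versus W measures the whole procedure: herbs, pressure on the acupoints, and expectation relative to an arm that knows it is untreated. P versus W measures the sham effect. A test of a three-level group factor rejects when any two arms differ, so P and T both beating W is enough.

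The plan expects P to beat W. A trial in which the herbs add nothing could therefore give a significant group test and a significant T versus W result, and the protocol has no sentence saying how to read that. The Discussion says the results should provide evidence of the effectiveness of Tian Jiu, so the conclusion rests on a choice of contrast that could be made after the data are seen.

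**Working it through.** **The plan's own figure.** The stated formula is n = 2λ / (2·asin√Pt − 2·asin√Pw)². With Pt = 0.30 and Pw = 0, the bracket is 1.159. At two-sided 0.025 and 80 % power, λ = 9.505 (1 df), so n = 2 × 9.505 / 1.159² = 14.1, i.e. 15 per group (18 with the 2-df λ). The stated 38 is not reproduced; it would need λ = 25.5. That is a separate matter. What counts here is that T versus W is the only contrast entered.

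**Inputs.** 38 evaluable and 46 recruited per arm; two-sided 0.05; rates of 30 %, 15 % and 0, all from the protocol. It gives no SD for the Total Nasal Symptom Score (TNSS), so effects on the continuous scale are assumptions.

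**Herbs add nothing, responder scale (T = P = 15 %, W = 0).** W has no responders, so T versus W depends only on the T count.

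- Chi-square without correction needs at least 4 responders in T (statistic 4.22 at n = 38 and 4.18 at n = 46; 3 responders give 3.12 and 3.10).
- Fisher's exact test needs at least 6 (P = 0.025 and 0.026; 5 responders give 0.054 and 0.056).

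| n per arm | T vs W, chi-square: Pr(X ≥ 4) | T vs W, Fisher: Pr(X ≥ 6) |
|---|---|---|
| 38 | 0.842 | 0.515 (simulated 0.517) |
| 46 | 0.929 | 0.707 |

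In the same setting T versus P is significant in about 5 % of simulated trials by chi-square and 3 % by Fisher, counting both directions.

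**Herbs add nothing, continuous scale (T = P = d, W = 0, d in residual SD units).** The group F test has 2 and 3n − 4 df. Its noncentrality is n × Σ(μ − mean)² = n × (2/3)d². At d = 0.5 this is 38 × 0.1667 = 6.33, or 46 × 0.1667 = 7.67.

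| d (assumed) | F test significant, n = 38 | n = 46 |
|---|---|---|
| 0.3 | 0.246 | 0.293 |
| 0.5 | 0.596 | 0.687 |
| 0.8 | 0.954 | 0.982 |

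**How the missing rule matters.** For d = 0.5, n = 38 and each test at two-sided 0.05 (simulated), with T truly equal to P:

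- T beats P or T beats W: 59 %
- T beats both: 2.4 %
- T beats P: 2.5 %

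**Power of T versus P on the plan's rates (30 % versus 15 %).** The arcsine difference is 1.159 − 0.795 = 0.364. Power is Φ(0.364 × √(n/2) − 1.960):

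- n = 38: Φ(1.586 − 1.960) = 0.354
- n = 46: Φ(1.745 − 1.960) = 0.415

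For 80 % power at 0.05, n = 2 × 7.849 / 0.364² ≈ 119 per arm.

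**The case against.** **No success rule is written.** A reader might infer that the protocol makes the three-arm F test, or T versus W, the criterion for efficacy. It does not. It names a model, and that same ANCOVA yields the T minus P contrast. The model sentence quoted concerns items and subscales, and whether comparisons are global or pairwise is not stated. The defect is an open choice, not a wrong rule.

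**The authors saw the problem.** The Objective joins the comparators with *and*, which can be read as requiring both; the check shows that this reading would guard against the error. The Discussion explains the third arm by the sham effect. So a reader should not infer that the investigators would ignore their placebo arm and report an inert herb as effective. But neither text is a decision rule, and the sample size points the other way.

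**Contrasts are often left to an analysis plan.** That is fair for their detail. Here, however, the protocol itself ties significance to T versus W, the contrast that cannot separate the herbs from the sham effect it expects.

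**The rate calculations are not the planned analysis.** This stands. With 15 % versus 0 and 38 per arm, pooled expected responders are about 2.9 per arm, too few to rely on chi-square, so the Fisher figures are the safer ones. The continuous figures fit the planned analysis better but rest on assumed effects.

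**It is called a pilot, and T versus W is a legitimate question.** Both are true. T versus W answers a question about the whole procedure and should be labelled so.

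**Conclusion.** The concern holds in this form: no deciding contrast is named, the only sized contrast is T versus W, and both T versus W and the group test can readily be significant when T equals P. The size is about 84–93 % (chi-square) or 52–71 % (Fisher) for T versus W at 15/15/0 %, and 60–69 % for the F test at an assumed 0.5 SD. The 25–98 % range over 0.3–0.8 SD shows how far the last figure depends on that assumption.

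One further inference should be avoided. On the plan's 30/15/0 % rates, T versus W is significant and T versus P is not in about 59–65 % of simulated trials by chi-square. Because T versus W is almost always significant at those rates, this is essentially one minus the power of T versus P. It shows that the unaddressed result is the likeliest one; it does not measure false claims of efficacy.

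**What to change.** In Data processing and analysis, state:

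1. Efficacy of Tian Jiu beyond sham is concluded only if the ANCOVA-adjusted T minus P contrast in change in weekly-average TNSS at the end of treatment (week 4) is significant at two-sided 0.05.
2. T versus W is tested next, in fixed order. If T versus P is not significant, the T versus W estimate and interval are reported as the effect of the whole patch procedure.
3. P versus W is descriptive.
4. The three-arm F test alone supports no efficacy claim.

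This is one paragraph, with no new patients or data. The Trial status section says no patient has begun treatment, so it can be written in time.

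The price should be stated with it. The Sample size section supports only T versus W. T versus P has about 35–41 % power at 0.05 with 38 to 46 per arm, against the roughly 119 evaluable per arm needed for 80 %. A non-significant T versus P result is therefore inconclusive, not evidence that the herbs do nothing. T versus W would often go without a formal test, and a result positive only against waitlist could not be called efficacy of the herbs.

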### Data collection and handling of withdrawal and dropout

This is a 9-week clinical trial, in which subjects must take TJ for 8 weeks, attend five assessment visits, complete a set of questionnaires, and stop taking other medications for symptom control. All collected information will be input into a computer by a RA. In the meantime, all the files will be stored in numerical order. Participant files will keep in storage for 5 years.

Considering maximization of participants’ compliance, we will firstly run a thorough consent process for all subjects by interpreting the details of the trial schedule, potential adverse events, and the responsibilities of researchers and participants. In addition, before every visit, a RA will contact the subject to re-confirm the schedule. If a participant shows signs of wanting to withdraw, we would try to understand the possible reasons and aim to find the best option for encouraging the participant to remain in the study.

